### 2.4. Acupuncture Treatments

Two fixed acupuncture protocols, true acupuncture and control acupuncture, are used in the study. The rationale of true acupuncture is based on existing data from experimental studies and on previous RCT in women with PCOS [20, 22]. The control acupuncture is chosen in contrast to true acupuncture and designed in such a way that it is thought to be less effective for ovulation induction. The two acupuncture protocols follow the STRICTA recommendations [29]. 

Clinical experience and training of acupuncturists may affect the outcome [30]. To assure that the intervention is performed in a standard manner, all acupuncturists with TCM certificate and 1 year experience receive a study specific theoretical course and a study specific practical training, totally 3 times before the beginning of the study, 1–3 days per time, and 1 time, four hours after one month of the study beginning. All acupuncturists have to pass the theory and practical tests. In China, acupuncturists perform acupuncture in over 50 patients per day, thus they will rapidly be experienced. Furthermore, while they are trained for only a short time for this study acupuncture protocols, they are graduate students in Chinese medicine and have received general acupuncture training during their studies. In this study, 35 acupuncturists have been trained both in theory and practice of acupuncture, and there is at least one designated acupuncturist at each participating site. 

All participants receive acupuncture treatment twice a week and each treatment session can be separated by an interval of 2–4 days, with a maximum of 32 treatment sessions during 16 weeks. Each treatment session lasts for 30 minutes. Acupuncture treatment will start on day 3 after a spontaneous period or a withdrawal bleeding following progestin, when starting with CC/placebo tablet. Participants will be contacted by phone if they miss the appointment as scheduled. If they miss appointments in the early part of the cycle, more appointments will be arranged in the later part to compensate the missing part. Missed appointments will be clearly documented in the record for analysis later. If the participants miss 6–8 acupuncture treatments (3-4 weeks), she should be scheduled not to take CC or CC placebo and have this treatment cycle “cancelled” until she can get acupuncture. 

In true acupuncture, needles are made of stainless steel (Hwoto, Suzhou Medical Appliance Fact., Suzhou, China); 0.25 × 30 mm and 0.30 × 40/50 mm needles are inserted to a depth of 15–35 mm in acupuncture points located in abdominal and leg muscles with same somatic innervations as the ovaries and uterus [31]. Two sets of acupuncture points alternated every other treatment. The first set of acupuncture points consists of conception vessel (CV) 3, CV 6, and stomach (ST) 29 bilaterally and in the muscles below the knee, spleen (SP) 6, and SP 9 bilaterally; all segmental points with somatic innervations correspond to the ovaries and the uterus (Table 1). Needles are also placed in extrasegmental acupuncture points that do not innervate the ovaries and uterus: large intestine (LI) 4 bilaterally and governor vessel (GV) 20. Abdominal and leg points were selected because they have been demonstrated to increase ovarian blood flow response [13, 14]. Points in hands and head have been used in previous studies [20] and were selected to potentiate the effect of the segmental points. Furthermore, they have been demonstrated in experimental studies to act via central nervous system [32]. 

A total of 11 needles are placed, and all are stimulated manually by rotating the needle quickly with thumb and forefinger to evoke needle sensation (de qi) once when inserted. De qi reflects activation of afferent nerve fibers and can be described as numbness, distension, or electrical tingling. The points CV 3, CV 6, ST 29, SP 6, and SP 9 are thereafter connected to electrical stimulator (AS Super 4 Digital, schwa-medico GmbH, Ehringshausen, Germany) and stimulated with low-frequency, 2 Hz, 0.3 ms pulse length and the intensity is adjusted to produce local muscle contractions without pain or discomfort. Needles not connected to the electrical stimulator are manually stimulated by rotating the needle to evoke needle sensation every 10 min, in a total of 4 times. If the sensation of de qi does not occur, manual manipulation techniques can be applied to promote it (such as “plucking,” “shaking,” or “trembling”). The second set of acupuncture points consists of 13 needles placed in segmental abdominal points; ST 25 and 29 bilaterally (electrical stimulation) and CV3 and CV6 (manual stimulation), leg points; SP6 and liver (LR) 3 bilaterally (electrical stimulation). Extrasegmental points are pericardium (PC) 6 bilaterally and GV20 (both manual stimulation). 

In control acupuncture, two needles will be inserted superficial to a depth of <5 mm in each arm, one in each shoulder and one in each upper arm at nonacupuncture points, without any stimulation (Table 1). Needles are made of stainless steel (Hwoto, Suzhou Medical Appliance Fact., Suzhou, China), 0.20 × 20 mm. Electrodes will be attached to the needles and the stimulator is turned on at an intensity of zero (no active current) in order to mimic electrical stimulation in the true acupuncture group. No stimulation of the needles is performed. 

Participants are monitored weekly by urinary pregnancy test and serum progesterone levels. The dose of oral medication may be increased by 50 mg in the absence of ovulation or maintained in the presence of ovulation. The maximum dose of CC will not exceed 150 mg/cycle. The treatment lasts for up to 4 month cycles. 

### 2.5. Study Specific Visits and Procedures

Each specific visit and measurement is summarized in Table 2. Baseline measures include fasting FSH, LH, total testosterone (T), estradiol (E2), sex hormone binding Globulin (SHBG), dehydroepiandrosterone sulfate (DHEAS), glucose and insulin concentrations, cholesterol, triglycerides, high-density lipoprotein cholesterol (HDL-C), low-density lipoprotein cholesterol (LDL-C) and height, weight, hip, waist measurements, and vital signs. Neither cervical mucus nor endometrial lining will be monitored in this large clinical trial as these are not routinely monitored in clinical practice. Also questionnaires for assessments of health related quality of life (QOL) are filled in: the short form 36 (SF 36) [33], the Polycystic Ovary Syndrome Questionnaire (PCOS-QOL) [34], and the Chinese Quality of life (ChQOL) [35]. Questionnaires for symptoms of anxiety and depression are Zung Self-Rating Anxiety Scale (SAS) [36] and Zung Self-reported Depression Scale (SDS) [37]. All questionnaires used in this trial are validated scales. 

The TCM diagnosis will be made by an experienced TCM doctor in each participating site according to a standard questionnaire. Syndrome differentiation in TCM is the comprehensive analysis of clinical information gained by the four main diagnostic TCM procedures: observation, listening, questioning, and pulse analysis [38]. In PCOS, patients are empirically differentiated to be four categories: (1) phlegm-dampness syndrome, (2) blood stasis syndrome, (3) phlegm and blood stasis, and (4) liver stagnation [39]. The TCM diagnosis will not affect the treatment protocol, and it will enable us to explore its effect on the treatment success in a secondary analysis.

All baseline measures will be repeated in all subjects at the end of visits. Blood samples (including the safety labs) will be collected and shipped to the core lab. Credibility check questionnaires are completed on the third acupuncture treatment and the last acupuncture treatment [40–42].

### 2.6. Responders

Responders are defined as having at least one weekly elevated serum progesterone level indicative of ovulation, that is, >3 ng/mL [43]. A woman who has ovulated will be followed weekly until she has a period or a positive pregnancy test. Responders will continue at the same dose of CC or placebo until pregnancy, or a total of four cycles are reached.

### 2.7. Nonresponders

No response is defined after 4 weeks of CC/Placebo CC administration and true acupuncture/control acupuncture with 3 consecutive weekly negative progesterone and hCG levels. Ovulation will be monitored by weekly serum progesterone level and ultrasound monitoring will not be performed as in a previous study [4]. Then during the fifth week a higher dose consisting of one more tablet per day (up to 3 tablets per day at third or fourth cycles, if they remain nonresponders) is given for 5 days, together with 2 weekly sessions of acupuncture. If there is no period after 3 weeks and the woman is not pregnant, CC 100 mg or 2 placebo tablets will be given daily from day 3 to day 7. If there is again no period after 3 weeks and the woman is not pregnant and not ovulating by progesterone levels, CC 150 mg or 3 placebo tablets will be given daily from day 3 to 7. The same CC dose will be continued in the next cycle if she is shown to have ovulation. A maximum of CC 150 mg or 3 placebo tablets daily are to be given even if she does not ovulate during the study period. Nonresponders will not receive progesterone for withdrawal bleeding before a higher dose of CC unless at discretion of the site investigator.

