### 2.8. Pregnancy Visits

Serum progesterone and hCG levels are determined locally at sites to document ovulation and pregnancy during weekly visit for acupuncture treatment. Serial serum hCG level will be checked on a weekly basis if pregnant. Serum beta hCG > 10 IU/L is usually considered to be positive and indicates pregnancy. Pelvic ultrasound will be arranged to confirm the number and location of the gestational sac(s) when serum hCG is around 1500 IU/L or clinically indicated. Then pelvic ultrasound will be arranged every two weeks until viability of the pregnancy is determined by visualization of fetal heart motion. Pregnant subjects will be referred to the obstetrics unit and follow-up scans will be performed at week 18–24, 32, and 36 or at the discretion of the obstetrician.

We do not encourage the pregnant subjects to take any drugs during pregnancy. However, in Mainland China, pregnant women may be given many medications including TCM when they present with the risk of miscarriage. In this trial, pregnant women who presents with threatened miscarriage or are considered to have a significant risk for miscarriage can be given oral Duphaston (10 mg twice a day, Solvay Pharmaceuticals B.V.) till 12 weeks of gestation or 1 week after the vaginal bleeding stops as some studies [44–46] have shown benefit of Duphaston in threatened miscarriage. This information will be documented in the record form. No other medications including hCG, herbal medications, and acupuncture will be given by the investigators. 

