### 2.12. Data Analysis

The primary outcome is the live birth rate. Secondary outcomes include (1) ovulation rate; (2) ongoing pregnancy rate at gestation 8–10 weeks; (3) multiple pregnancy rate; (4) miscarriage rate: loss of an intrauterine pregnancy before 20 completed weeks of gestation; (5) change in hormonal profile: FSH, LH, T, SHBG, and DHEAS; (6) change in metabolic profile: glucose and insulin concentrations, cholesterol, triglycerides, HDL-C, and LDL-C; (7) side effect profile; (8) change in QOL; (9) change in symptoms of anxiety and depression; and (10) credibility assessments.

The analysis will use an intent-to-treat (ITT) approach to examining differences in the live birth rates among the four treatment arms. Primary efficacy analysis will be done by comparing the treatment groups with respect to the primary outcome of live birth using the Pearson Chi-square test. For the secondary, supportive analysis, we will fit a logistic regression model to compare the treatment arms with respect to the primary outcome of live birth, adjusting for other factors such as randomization stratification of study site and prior exposure to study medications. The analysis of other secondary outcomes measured over time will entail the application of statistical methods that have been developed for correlated data since repeated observations will be made over time on each individual. For secondary outcomes such as hormone levels, a linear mixed-effects model will be fit where the main independent variables will be treatment group, time, and their interaction as well as the designed randomization stratification factors as covariates. Logistic regression models will be used in secondary analyses to evaluate the predictive value of treatment arm, clinical site, prior exposure to CC, body mass index, and other explanatory variables on binary outcomes (e.g., singleton live birth, abortion). Cox proportional hazards models and a Kaplan-Meier method will be applied to compare time to pregnancy in the treatment groups. 

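### Ovulation is scored from any one weekly serum progesterone above 3 ng/mL, but sites may by exception give non-responders progesterone, and no rule keeps later samples out of the ovulation rate

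*Protocol article*

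**What the plan says.** Section 2.6 of the protocol article classes a woman as a responder if she has "at least one weekly elevated serum progesterone level indicative of ovulation, that is, >3 ng/mL". One value is enough, and the rule does not mention where the hormone came from or when the sample was drawn.

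Section 2.7 defines non-response after 4 weeks of treatment "with 3 consecutive weekly negative progesterone and hCG levels". It makes the assay the only evidence of ovulation: "Ovulation will be monitored by weekly serum progesterone level and ultrasound monitoring will not be performed as in a previous study". It then sets a default with an exception: "Nonresponders will not receive progesterone for withdrawal bleeding before a higher dose of CC unless at discretion of the site investigator".

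Sampling is weekly throughout treatment (2.4, last paragraph; Table 2), and section 2.8 adds: "Serum progesterone and hCG levels are determined locally at sites to document ovulation and pregnancy during weekly visit for acupuncture treatment". In section 2.12 the list of secondary endpoints opens with this outcome: "Secondary outcomes include (1) ovulation rate".

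The article uses two terms for the agent that brings on a bleed. Section 2.4 speaks of progestin before the first cycle; section 2.7 speaks of progesterone in non-responders.

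**The concern.** Section 2.7 allows, by exception, a drug with the same name as the analyte that defines the outcome. If a non-responder receives it and her next weekly sample exceeds 3 ng/mL, the value reflects the drug, yet it meets the printed rule for ovulation. No second measure, such as ultrasound, would reveal the error.

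The error can go only one way. Only women who have not ovulated are exposed, so it can add ovulations but not remove them. An arm with less true ovulation has more women at risk. At stake is the size of the arm differences in ovulation rate, which would be drawn toward zero.

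**Working it through.** The article gives no ovulation rate by arm, and no power or significance level for this outcome, so there is no figure of its own to reproduce. The check sets the rules side by side and then works out the direction and form of the error.

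**Can a drug-derived value be scored as ovulation?**

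1. Rule: one weekly value above 3 ng/mL (2.6).
2. Other evidence of ovulation: none (2.7).
3. Exposure: allowed by exception in women already classed as non-responders (2.7).
4. Later samples: yes, weekly (2.4, 2.8, Table 2).
5. Exclusion of samples drawn after such a dose: none in the article.

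Applied literally, the rule can count such a value.

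**Direction and form.** Let p be the true ovulation rate in an arm. Let f be the share of non-ovulating women who are treated and then sampled while the drug is measurable.

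- Observed rate: p′ = p + (1 − p)f
- Difference between two arms with the same f: p₁′ − p₂′ = (p₁ − p₂)(1 − f)

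**Illustration.** The 73% is the per-cycle rate under clomiphene citrate (CC) from published results, quoted in the Introduction. The placebo-CC rates of 20%, 30% and 40% and all values of f are assumptions; the article gives neither.

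| Assumed placebo-CC rate | f | Observed rates | True difference | Observed difference |
|---|---|---|---|---|
| 20% | 10% | 75.7% vs 28.0% | 53 points | 53 × 0.90 = 47.7 |
| 20% | 25% | 79.75% vs 40.0% | 53 points | 53 × 0.75 = 39.75 |
| 30% | 10% | 75.7% vs 37.0% | 43 points | 43 × 0.90 = 38.7 |
| 30% | 20% | 78.4% vs 44.0% | 43 points | 43 × 0.80 = 34.4 |
| 40% | 10% | 75.7% vs 46.0% | 33 points | 33 × 0.90 = 29.7 |
| 40% | 25% | 79.75% vs 55.0% | 33 points | 33 × 0.75 = 24.75 |

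At f = 0 every difference is unchanged.

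**Is equal f reasonable?** Section 2.3 keeps investigators blind to CC, and only the acupuncturist (besides the data manager) knows the acupuncture assignment. Discretionary use among non-responders should therefore be similar across arms, though this is not guaranteed. Use may vary between sites, but randomization is stratified by site, so within a site with share fₛ the difference shrinks by (1 − fₛ).

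**The case against.** **This is detail left to fuller documents.** Section 3.1 mentions a manual of operations and case report forms, which are not shown and may hold an exclusion. That is a fair limit. But the article itself fixes both the scoring rule and the exception, and as printed they give a wrong classification. The rule is faulty, not merely brief.

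**The definition requires a value that indicates ovulation, and a value after dosing does not.** A careful reader might apply it so. But the sentence goes on to equate that qualifier with a level above 3 ng/mL, so the number decides.

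**Non-response is settled before any progesterone is given.** This stands. The three negative weekly values come first, and the exception concerns women already classed as non-responders. The risk is confined to later samples, drawn while the drug is measurable.

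**The agent may not be one the assay reads.** This also stands. If section 2.7 means the same as the progestin of section 2.4, and the assay does not detect it, the effect is nil. The article does not settle this.

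**A reader might infer that dose decisions are corrupted too**, since 2.7 says "The same CC dose will be continued in the next cycle if she is shown to have ovulation". The text does not support going that far. Progesterone is contemplated before a higher dose, when the step-up is already intended, and nothing ties the quoted sentence to a sample drawn after such a dose. What remains is that 2.4, 2.6 and 2.7 do not say how such a reading is treated for responder status.

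**Conclusion.** The point holds as a defect in the definition of a secondary outcome. As written, a progesterone value that follows a discretionary dose can be scored as ovulation. With similar use across arms, this pulls differences in ovulation rate toward zero by the factor (1 − f).

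The size is unknown. The default is that no progesterone is given, so f may be small, and it is zero if the assay does not read the agent. The table shows the form of the effect and does not forecast it; a reader should not take a loss of 10% or more as expected.

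A reader might also infer that the primary result is biased. The documents do not support that: live birth is not defined through serum progesterone and is not misclassified. This is a minor but worthwhile correction.

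**What to change.** 1. **Outcome definition.** For the ovulation rate, state that serum progesterone values drawn after any exogenous progesterone or progestin, up to the next bleed, do not count as ovulation. Classify that cycle from the values drawn before the dose.
2. **Data.** Record the product and date of each such dose with the concomitant medication, which Table 2 already has assessed weekly.
3. **Terms.** Reconcile progestin in 2.4 with progesterone in 2.7, so that it is clear whether the assay can read the agent used.
4. **Responder status.** Reconcile 2.4, 2.6 and 2.7 on how a reading taken after such a dose is treated. Which clinical rule applies is for the investigators; no dose or treatment rule is proposed here.

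The cost is one sentence in the definition and a product and date entry on the case report form. A few cycles will rest on fewer progesterone values.

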### 2.8. Pregnancy Visits

Serum progesterone and hCG levels are determined locally at sites to document ovulation and pregnancy during weekly visit for acupuncture treatment. Serial serum hCG level will be checked on a weekly basis if pregnant. Serum beta hCG > 10 IU/L is usually considered to be positive and indicates pregnancy. Pelvic ultrasound will be arranged to confirm the number and location of the gestational sac(s) when serum hCG is around 1500 IU/L or clinically indicated. Then pelvic ultrasound will be arranged every two weeks until viability of the pregnancy is determined by visualization of fetal heart motion. Pregnant subjects will be referred to the obstetrics unit and follow-up scans will be performed at week 18–24, 32, and 36 or at the discretion of the obstetrician.

We do not encourage the pregnant subjects to take any drugs during pregnancy. However, in Mainland China, pregnant women may be given many medications including TCM when they present with the risk of miscarriage. In this trial, pregnant women who presents with threatened miscarriage or are considered to have a significant risk for miscarriage can be given oral Duphaston (10 mg twice a day, Solvay Pharmaceuticals B.V.) till 12 weeks of gestation or 1 week after the vaginal bleeding stops as some studies [44–46] have shown benefit of Duphaston in threatened miscarriage. This information will be documented in the record form. No other medications including hCG, herbal medications, and acupuncture will be given by the investigators. 

### 2.9. End of Treatment Visit

At the end of study, a visit will be arranged for all women. The end of treatment visit should be performed as early as possible in pregnant women. A brief physical examination including acne and hirsutism assessment and a final assessment of adverse events and concomitant medications will be performed. Subjects will return the remaining study drug and their journal logs. All baseline measures will be repeated in all subjects. 

The blood samples done at the baseline visit and the end of the treatment visit will be shipped to the core laboratory for analysis. 

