### 2.10. Establishment of a Pregnancy Registry

The outcomes of all pregnancies will be followed after delivery or termination of gestation. We will review pregnancy and birth records of the mother and of the fetus to establish neonatal morbidity and mortality and the presence of fetal anomalies. We will extract from these records concomitant medical and obstetrical conditions, exposure information on all other medical products used, including prescription products, over-the-counter products, dietary supplements, vaccines, and insertable or implantable medical devices. We will file individual case reports for all congenital anomalies, which will be reported as serious adverse events. The ectopic pregnancies will be identified by serial hCG monitoring and pelvic ultrasound examination. The doctors performing pelvic ultrasound are blinded to the treatment groups.

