Adverse events will be categorized and percentage of patients experiencing adverse events and serious adverse events in this trial will be documented. Chi-square tests will be performed to examine differences in the proportion of total and categories of adverse events within each treatment arm. For each Data and Safety Monitoring Board (DSMB) report, a list and summary of the reported adverse events will be presented in a blinded fashion, unless otherwise formally requested. Unblinding of treatments will take place after all participants have delivered or reported final outcomes to the DCC or when there are medical emergencies.

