Sign consent	×										
History	×										×
Urine pregnancy test	×		×	×	×	×	×	×	×	×	
Physical examination	×										×
Transvaginal ultrasound	×										×
Semen analysis	×										
Hysterosalpingogram	×										
Safety eligibility lads	×										×
Fasting phlebotomy for study parameters		×									×
Depression, anxiety, and quality of life questionnaires	×										×
Credibility check questionnaire			×		×						×
Progesterone assay	×			×		×		×		×	×
HCG assay	×			×		×		×		×	×
Acupuncture treatments (twice weekly)			×	×	×	×	×	×	×	×	
Assess adverse events and concomitant meds				×		×		×		×	×

Credibility check questionnaires are completed on the third acupuncture treatment and the last acupuncture treatment.

HCG: HCG concentrations will be measured once a week during the study period. If serum HCG concentration is elevated above 10 IU/L, pelvic ultrasound will be arranged 2 weeks later for the number of the gestational sacs and the viability of the pregnancy.

**Table 3 tab3:** The respective live birth rates in each intervention.

Interventions	True acupuncture	Control acupuncture
CC	*A* = 25%	*B* = 15%
Placebo CC	*C* = 15%	*D* = 5%

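### Adverse-event observation ends earlier in women who conceive, and the planned comparison of patient percentages makes no allowance for this or for serious events that only pregnancies can produce

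*Protocol article*

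**What the plan says.** - Section 2.9 (End of Treatment Visit) sets the timing: "The end of treatment visit should be performed as early as possible in pregnant women". At that visit "a final assessment of adverse events and concomitant medications will be performed".
- In Table 2, the row "Assess adverse events and concomitant meds" is marked once a week during treatment and at the end-of-treatment visit. The table has no later column.
- Section 2.10 (Pregnancy Registry) continues beyond that visit: "The outcomes of all pregnancies will be followed after delivery or termination of gestation". Records are reviewed "to establish neonatal morbidity and mortality and the presence of fetal anomalies", and further: "We will extract from these records concomitant medical and obstetrical conditions, exposure information on all other medical products used".
- One kind of registry event is stated to count as a serious adverse event: "We will file individual case reports for all congenital anomalies, which will be reported as serious adverse events".
- Section 2.12 lists the side effect profile as secondary outcome 7. It plans to document the percentage of patients with adverse and serious adverse events, and adds: "Chi-square tests will be performed to examine differences in the proportion of total and categories of adverse events within each treatment arm". It mentions no allowance for length of observation.

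**The concern.** How long a woman is asked about adverse events depends on whether and when she conceives. Conception is the route to the primary outcome, and the plan projects that it will differ by arm. With equal weekly risk of, say, headache or hot flushes, the arm with more pregnancies would show a lower percentage of women affected simply because it is watched for less time.

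Congenital anomalies act in the opposite direction. They can be found only in women who conceive. With equal risk per birth, the arm with more births shows a higher percentage of randomised women with a serious event.

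A single percentage per arm thus mixes tolerability with fertility. The comparison at stake is secondary outcome 7, not the primary result.

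**Working it through.** The article gives no figure for adverse-event follow-up time, so there is none to reproduce.

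**Inputs from the article**
- Live birth rates p (Table 3): A 25%, B 15%, C 15%, D 5%. Their mean is (25 + 15 + 15 + 5)/4 = 15%, as Section 2.11 states.
- Treatment lasts up to 16 weeks (Section 2.4), with 250 women per arm (Section 2.3).

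**Assumptions, because the article gives no conception rate and no week for the early visit**
- Pregnancy loss L is 0-30%, the same in all arms, so the share conceiving is q = p/(1 - L).
- The early visit falls on average at week m, with m from 6 to 12. All other women are observed for 16 weeks. Dropout is ignored.

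**Step 1. Mean window per arm: (1 - q) × 16 + q × m**

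| Case | A | B and C | D | A/D |
|---|---|---|---|---|
| L = 0, m = 12 | 15.0 | 15.4 | 15.8 | 0.949 |
| L = 20%, m = 8 | 13.5 | 14.5 | 15.5 | 0.871 |
| L = 30%, m = 6 | 12.43 | 13.86 | 15.29 | 0.813 |

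For example, with L = 30% and m = 6, q in arm A is 0.25/0.70 = 0.357, and 0.643 × 16 + 0.357 × 6 = 12.43 weeks. Arm A is about 5-19% shorter than arm D.

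A against D is the widest contrast. For the two acupuncture contrasts the gap is roughly half:
- A against B: 15.0/15.4 = 0.974 to 12.43/13.86 = 0.897, so about 3-10% shorter.
- C against D: 15.4/15.8 = 0.975 to 13.86/15.29 = 0.906, so about 3-9% shorter.
- B against C: no difference, because the projected rates are equal.

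A cruder calculation gives a similar answer. Suppose conceptions are spread evenly over four cycles, with windows of 5, 9, 13 and 17 weeks (mean 11) against 17 weeks for other women, and no losses. Then A = 0.75 × 17 + 0.25 × 11 = 15.5 weeks and D = 0.95 × 17 + 0.05 × 11 = 16.7 weeks, a ratio of 0.93.

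**Step 2. Effect on the percentage with an event**

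Take the same constant weekly hazard in every arm, h = -ln(1 - b)/16, where b is the proportion affected over a full 16 weeks. The observed proportion is (1 - q) × b + q × (1 - exp(-h × m)).

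| b | Case | A | D | Gap in points |
|---|---|---|---|---|
| 20% | L = 0, m = 12 | 18.9% | 19.8% | 0.9 |
| 20% | L = 30%, m = 6 | 15.7% | 19.1% | 3.4 |
| 40% | L = 0, m = 12 | 38.0% | 39.6% | 1.6 |
| 40% | L = 30%, m = 6 | 31.9% | 38.4% | 6.5 |

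**Step 3. Congenital anomalies as serious adverse events**

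With risk r per birth equal in all arms, the percentage of randomised women affected is r × p. The ratio of A to D is 25/5 = 5 whatever r is. The absolute size depends on r, which the article does not give:
- r = 1%: 0.25% against 0.05%
- r = 3%: 0.75% against 0.15%
- r = 5%: 1.25% against 0.25%

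At r = 3% this is 250 × 0.0075 = 1.9 women in A and 250 × 0.0015 = 0.4 in D.

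**The case against.** The strongest reply is that this is an end-of-treatment visit. Section 2.6 continues tablets only until pregnancy, and Section 2.8 says that investigators give no acupuncture in pregnancy. Observation therefore ends at about the time exposure ends, and a percentage per randomised woman is a legitimate description of what each strategy brings. This stands, and it is why the percentages should stay. It does not make them a comparison of tolerability over equal time.

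It can also be said that the distortion is small, that it rests on assumed conception timing and loss, that exposure-adjusted rates often appear in an analysis plan, and that testing by category would show anomalies separately. The size is indeed modest. But the article does state the analysis it intends, and that analysis has no time element.

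Three stronger readings are tempting, and the document does not support them:
- **Harms of pregnancy go unrecorded after the early visit.** Section 2.8 provides weekly hCG, ultrasound until viability and later obstetric scans. Section 2.10 follows every pregnancy to its outcome through records, including ectopic pregnancy. Section 2.12 makes miscarriage and multiple pregnancy secondary outcomes, and Section 3.3 allows nine months of pregnancy follow-up. Weeks of gestation after the visit are not weeks without collection, and multiple pregnancies are not lost.
- **Serious registry events other than anomalies cannot reach the DSMB.** Section 3.2 has the DSMB review any serious adverse event, without a time limit. That anomalies are reported shows that serious-event reporting does not close at the early visit. The detailed route may stand in the full protocol or the manual of operations.
- **The chi-square is meant to be run inside each arm.** Read literally, the sentence says so, but a comparison between arms is the natural intention. This is a wording slip.

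**Conclusion.** The point holds in a limited form. Section 2.9 and Table 2 make the observation window for general adverse events depend on conception, and the test stated in Section 2.12 does not allow for it. If the arms differ as Table 3 projects, the window is shortest in arm A: about 5-19% shorter than in D, and about 3-10% shorter across the acupuncture contrasts. At equal risk this lowers the observed percentage in A relative to D by about 1 to 3 points for an event affecting 20% of women over 16 weeks, and by about 2 to 6 points for one affecting 40%. Anomalies push the serious-event percentage the other way, fivefold in relative terms but by only one or two women per arm at an assumed 3% per birth.

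These sizes rest on the Table 3 projections, the assumed range of losses and visit weeks, a constant hazard and no dropout. If the arms do not differ in pregnancy, the distortion vanishes. The primary outcome is unaffected.

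**What to change.** 1. Keep the percentages of randomised women with adverse and serious adverse events.
2. Add treatment-phase adverse events per woman-week of observation, by arm, with each woman's time running to her last adverse-event assessment. Read the two together: a rate per woman-week can mislead the other way if events cluster early in treatment.
3. Tabulate pregnancy, fetal and neonatal events from the existing registry separately, including the anomalies filed as serious adverse events. Give them per randomised woman and per pregnancy or birth, noting that the latter denominator is formed after randomisation and is not a randomised comparison.
4. Word the chi-square sentence in Section 2.12 as a comparison between treatment arms.

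The cost is one or two extra tabulations and a few lines of text. No visit, procedure or new data item is needed.
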